### Data cleaning and checking

Data was recorded originally in hardcopy then entered into a purpose built ACCESS database. All data entry was checked for accuracy by two researchers and any errors recorded and corrected. A Dietitian researcher checked the accuracy of FoodWorks data entry against the computed records prior to their entry into the ACCESS database.

### Data analysis

Outcome measures collected at baseline will be compared to those at 12 months (after adjusting for baseline weight) to assess intervention effects and compared with measures at 24 months (end phase 2) to assess whether the intervention effects were maintained. Analyses will be conducted using the intention to treat principle, and performed using SPSS version 19 (IBM). All variables will be checked for plausibility. Continuous variables will be assessed for normality. Independent sample t-tests and chi-squared tests will be conducted on continuous and categorical variables (respectively) to check they do not vary by intervention group at baseline, and by completers versus attriters. Analysis of covariance will be used to examine whether the intervention groups differed significantly in weight at each of 12 and 24 months after adjusting for baseline weight. Behaviour changes in diet and physical activity will be assessed as secondary outcome measures using analysis of covariance to determine whether the MI and SDI groups differed significantly in dietary or physical activity behaviours at 12 months. Results will be stratified for baseline BMI category.

Logistic regression analysis will be performed to assess whether categorical variables, such as smoking status significantly influenced weight. The visceral adipose tissue variable will be assessed for between group differences at 12 and 24 months using independent sample t-tests, and analyses stratified by BMI category to determine whether the results differed for the healthy weight and overweight women. Sensitivity analyses will be conducted to determine the effects on the outcomes of different methods of treating loss to follow-up (last observation carried forward versus imputation). The relationship between weight outcomes and compliance with the diet and physical activity behaviours will be assessed using mediation analysis [55].

A per protocol analysis will be conducted on women who adhered to the requirements of their assigned group. Adherent women are defined as those who completed all required eating and physical activity diaries over the 12-month period and attended all assessment sessions, regardless of assigned group, and who attended all five health professional consultations for the MI group. Results of the protocol adherent group will be compared with non-adherers in each group, that is, those who did not meet the adherence recommendations.

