**Methods and design:**

The study is a parallel-group RCT consisting of 12 months of intervention (Phase 1) and 12 months of monitoring (Phase 2). Non-obese pre-menopausal healthy females 44–50 years of age were screened, stratified according to Body Mass Index (BMI) category (18.5-24.9 and 25–29.9 kg/m^2^) and randomly assigned to one of two groups: motivational interviewing (MI) intervention (n = 28), or a self-directed intervention (SDI) (control) (n = 26). The MI intervention consisted of five consultations with health professionals (four with a Dietitian and one with an Exercise Physiologist) who applied components of MI counselling to consultations with the women over a 12 month period. The SDI was developed as a control and these participants received print materials only. Outcome measures were collected at baseline, three, 12, 18 and 24 months and included weight (primary outcome), waist circumference, body composition, blood pressure, plasma markers of metabolic syndrome risk, dietary intake, physical activity and quality of life. Analysis of covariance will be used to investigate outcomes according to intervention type and duration (comparing baseline, 12 and 24 months).

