While there is a substantial body of evidence showing that weight loss in the obese reduces cardiovascular risk, the body of evidence on weight gain prevention interventions is scant [17], with only one RCT investigating whether weight gain prevention in pre-menopausal women can mitigate the increase in cardiovascular risk usually associated with menopause [18,19]. The Women’s Healthy Lifestyle Project conducted in the United States was designed to prevent weight gain and increased cardiovascular risk associated with menopause [18,19]. Pre-menopausal women (44–50 y, N = 535) randomized into a lifestyle intervention group (15-session diet and exercise education program followed by a maintenance program) lost on average 0.1 (5.2) kg after 54 months compared with a gain of 2.4 (4.9) kg in the assessment-only group [19]. While the trial showed that it was possible to prevent menopausal weight gain and to limit the typical post-menopausal rise in low density lipoprotein (LDL) cholesterol, the researchers acknowledged that the 15-session intervention held over 20 weeks was labour intensive and required a substantial time commitment from participants [20]. There is a need for the development of less intensive interventions that could feasibly be implemented on a population basis.

While women are known to attempt weight control (defined as weight maintenance for those of healthy weight and weight loss for the overweight) [21], self-directed efforts have not prevented population weight gain. Data from over 12,000 mid-age women in the population-wide Australian Longitudinal Study on Women’s Health showed 70% of participants reported behaviours aimed at losing weight or preventing weight gain, but they were mostly unsuccessful [21]. In the first two years of the study, the women without surgical menopause gained a mean (SD) of 1.04 (4.7) kg [22], and the cohort continued to gain weight at 0.5 kg/year over the next three years [23]. In a study of the weight control practices used by the women [21] the only group who managed to successfully prevent weight gain included a commercial program in addition to the typical public health strategies of 'cutting down on the size of meals and snacks plus cutting down on fats and sugars plus exercise’. This demonstrates the need for population based interventions that provide the face-to-face support typical of commercial programs, in addition to the more traditional awareness raising and education strategies.

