Women in both groups received tailored, written weight control goals and diet and physical activity behaviour change goals and strategies that were developed individually for each participant by health professionals according to the results of their assessment. The documentation reiterated the weight control message, and then guided the participant on how to achieve change. For SDI participants not meeting recommendations, the behaviour change goal and strategy was documented on their goal sheet and mailed to them. For example, “Aim to eat 2 serves of fruit per day. Some suggestions of how you could achieve this may include: incorporate 1 serve of fruit into your afternoon snack, try adding dried or fresh fruit to your muesli and yoghurt for breakfast, try having 1 serve of fruit with yoghurt for dessert”. MI participants were empowered to negotiate their own goals and strategies with a health professional in a face to face consultation. For example, the participant was asked to identify if increasing fruit intake was a behaviour they would like to change. If the participant agreed, they were asked to identify a realistic fruit goal (e.g. eating 1 serve of fruit per day). Next they were asked how they may go about achieving this goal. It was their responsibility to identify strategies to change their behaviour. If exhaustive exploration of their own ideas yielded no feasible strategies, the health professional sought consent to provide advice and recommended a suite of potential strategies from which the participant could choose.

The weight gain prevention advice was based on 10 messages (seven dietary intake messages and three physical activity messages - see Table 2) developed using available evidence on the factors contributing to weight gain in mid-age women [23,31,37-39] and national recommendations for this age group [30,40] as shown in Table 2. Messages were phrased using positive language seeking to enhance self-efficacy, which is the confidence to perform a specific behaviour [35]. The phraseology emphasised that change is a possibility, for example *“****You can avoid ****gaining weight during this life stage by…”.* The messages were pre-tested in an earlier study via telephone interview with a national sample of 40 women to ensure that they were clear, relevant and consistent with acceptable communication.

**Table 2 T2:** **Ten messages aimed at preventing weight gain**^
**1 **
^**in mid-age**

** *Target behaviour* **	** *Message wording* **

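### For waist, body fat and muscle, blood pressure, plasma markers and SF-36, the Data analysis section words the intervention effect as a change from baseline, not as an MI versus SDI difference

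*Protocol article*

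**What the plan says.** The Abstract (Methods and design) names weight as the primary outcome and lists the others as "waist circumference, body composition, blood pressure, plasma markers of metabolic syndrome risk, dietary intake, physical activity and quality of life". It then says: "Analysis of covariance will be used to investigate outcomes according to intervention type and duration (comparing baseline, 12 and 24 months".

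The Data analysis section opens with a sentence on outcome measures in general: "Outcome measures collected at baseline will be compared to those at 12 months (after adjusting for baseline weight) to assess intervention effects". The sentence goes on to a comparison with 24-month measures, to judge whether effects were maintained. It names no arm, and its only covariate is baseline weight.

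The same section then gives these explicit between-arm analyses:

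- Weight: "Analysis of covariance will be used to examine whether the intervention groups differed significantly in weight at each of 12 and 24 months", adjusted for baseline weight.
- Diet and physical activity: ANCOVA "to determine whether the MI and SDI groups differed significantly in dietary or physical activity behaviours at 12 months".
- Visceral adipose tissue: independent-sample t-tests between groups at 12 and 24 months.

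No later sentence in the section names a test for waist, percentage fat, skeletal muscle mass, blood pressure, plasma markers or SF-36 scores.

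The control arm is active. The section on theoretical framework and intervention materials says: "Women in both groups received tailored, written weight control goals and diet and physical activity behaviour change goals and strategies". Under Phase 1, women in the self-directed (SDI) arm are mailed their assessment results, individualised advice and the same support materials as the MI arm.

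**The concern.** An intervention effect in a randomised trial is a difference between arms. The opening sentence of Data analysis instead compares two time points and calls the result an intervention effect. Where a later sentence supplies a between-arm test, this does no harm. For the outcomes without one, the opening sentence is all that an analyst working from this section has.

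The distinction matters in this trial because both arms receive tailored goals, feedback of results and the same printed materials, and both are followed over one to two years of midlife. Change from baseline can occur in both arms without any effect of MI. If that change were reported as an intervention effect, MI would be credited with the passage of time or with advice that the controls also received.

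The covariate is a second weakness. If the opening sentence is read generously as ANCOVA for every outcome, the only adjustment it names is baseline weight. For blood pressure or LDL cholesterol, the useful covariate is the baseline value of that same measure.

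**Working it through.** **1. What each outcome is given in the Data analysis section**

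| Outcome | Explicit between-arm test | Otherwise covered by |
|---|---|---|
| Weight | ANCOVA, 12 and 24 months | opening sentence |
| Diet, physical activity | ANCOVA, 12 months | opening sentence |
| Visceral fat | t-tests, 12 and 24 months | no baseline measure exists |
| Waist; percentage fat and muscle mass; blood pressure; plasma markers; SF-36 | none | opening sentence only |

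Under Anthropometry, visceral fat is measured only at 12, 18 and 24 months, so a baseline comparison could not apply to it.

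**2. The opening sentence beside the abstract**

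Data analysis compares baseline with follow-up and adjusts for baseline weight. The abstract describes ANCOVA by intervention type and by duration, with baseline among the compared times. The abstract therefore has an arm factor that the opening sentence lacks. It also treats baseline as a compared level, whereas the weight ANCOVA in Data analysis uses baseline as a covariate. The two places do not describe the same model.

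**3. Illustration of the literal reading**

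The plan states no figure on this point, so there is none to reproduce. Inputs:

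- 22 women per arm, the number required per group in the Sample size section before the attrition allowance.
- No true MI minus SDI difference (assumed).
- A change δ shared by both arms, in units of the SD of change. The documents give no SDs for these outcomes, so δ is assumed and 0.3 and 0.5 are shown.
- A two-sided 5% paired t-test. This test is assumed; the document does not name it.

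Power of the paired test = P(|T| > t₀.₉₇₅,ₙ₋₁), where T is noncentral t with n − 1 degrees of freedom and noncentrality δ√n.

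- δ = 0.5, one arm: 0.5 × √22 = 2.35, critical value 2.08, power 61%.
- δ = 0.5, pooled: 0.5 × √44 = 3.32, critical value 2.02, power 90%.
- δ = 0.3, one arm: 0.3 × √22 = 1.41, power 27%.
- δ = 0.3, pooled: 0.3 × √44 = 1.99, power 49%.
- At least one arm significant, 1 − (1 − power)²: 1 − 0.39² = 85% at δ = 0.5; 1 − 0.73² = 47% at δ = 0.3.
- Exactly one arm significant at δ = 0.5: 2 × 0.61 × 0.39 = 48%.

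A between-arm t-test rejects in 5% whatever the value of δ, because the shared change cancels. A simulation of 40,000 trials gave 61%, 90% and 5% for one arm, pooled and between arms at δ = 0.5.

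**The case against.** The strongest reply is that the document elsewhere shows between-arm intent. The abstract lists these outcomes, and its next sentence applies ANCOVA by intervention type without restricting it to weight. Mentioning time as well does not remove the arm comparison. The opening sentence of Data analysis also covers weight, and weight then receives an explicit between-arm ANCOVA with the same adjustment, so for weight that sentence cannot mean a before-after test alone. It names no test and says neither paired nor within-group. The efficacy tests named for weight, diet and activity, and visceral fat all compare groups, and the Discussion speaks of low power for differences in secondary outcomes. All of this stands. It makes a between-arm analysis the likely intention.

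A reader might go further and infer that the plan discards randomisation for these outcomes, or that 61% to 90% is this trial's false-positive rate. The documents support neither. No paired test is specified, and the percentages show how an assumed test behaves under an assumed shared change. Nor do the documents establish lipid drift within this trial's follow-up: the Background remark that an intervention was able "to limit the typical post-menopausal rise in low density lipoprotein (LDL) cholesterol" comes from a trial followed for 54 months, whereas this one reads out at 12 and 24. Body composition as a whole is not uncovered either, since visceral fat has a group comparison.

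It can also be said that a condensed article need not give a model for every secondary outcome. That is fair as to omissions. The point here is narrower: a sentence that is present attaches the label of intervention effect to a contrast that cannot carry it.

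**Conclusion.** The point holds as a wording fault and an inconsistency. In Data analysis, the only sentence that reaches waist, percentage fat and muscle mass, blood pressure, plasma markers and SF-36 describes a baseline-to-follow-up comparison, adjusted only for baseline weight, as the assessment of intervention effects. Taken literally, that cannot isolate MI when the SDI arm is also advised. It also fits poorly with the abstract. Between-arm intent is likely but is not stated where the analysis is fixed.

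The consequence is limited. The primary weight analysis is a between-arm ANCOVA and is unaffected. The outcomes concerned are secondary and acknowledged as underpowered. The size of the problem cannot be taken from the documents; the 27% to 90% range depends on the assumed shared change of 0.3 to 0.5 SD, on 22 women per arm, and on paired tests being used. The sentence should be corrected because the correction is simple and removes a reading that would mislead.

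**What to change.** Replace the opening sentence of Data analysis with:

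> For waist, percentage fat, muscle mass, blood pressure, plasma markers and SF-36 scores, the intervention effect is the MI minus SDI difference at 12 and at 24 months, from ANCOVA adjusted for that outcome's own baseline value and BMI stratum; within-arm changes from baseline are descriptive and are not called intervention effects.

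Leave three things as they are:

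- The weight ANCOVA at 12 and 24 months. The Outcome measures section makes both times primary endpoints, so neither should be singled out.
- Diet and physical activity at 12 months. Food records and pedometers are described as issued only at baseline, 3 and 12 months.
- The group comparison of visceral fat, which has no baseline value to adjust for.

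Align the abstract sentence so that intervention type is the tested factor and baseline a covariate.

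The cost is one sentence in Data analysis and a small edit to the abstract. No new data, visits or software are needed. The downside is that within-arm p-values can no longer be reported as effects.

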### Randomization, blinding and quality assurance

Randomization was achieved using a computer-based random number sequence. Once written consent was obtained, participants were enrolled in the study. Baseline assessments were then completed and BMI status was checked and the women were categorised as healthy weight or overweight. At the end of the first assessment the enrolled women were given a participant identification number by a researcher ([name]). The numbers used were from a random allocation sequence generated by a statistician using a computer-based random number-producing algorithm to ensure an equal chance of allocation to each intervention group (the Plan procedure (Proc Plan) in the SAS statistical software package) in block lengths of six. The sequence was divided into two separate lists — one for each BMI category. [name] checked the BMI category of each participant at the conclusion of the first assessment, then allocated the participant to the next vacant number sequence on either the healthy weight list or the overweight list as appropriate. This ensured approximately equal numbers of healthy weight and overweight women were assigned to each intervention group. [name] remained blinded to group assignment. A separate version of each list, with intervention group appearing next to each identification number was only given to one researcher ([name]) who was unable to remain blinded after baseline measures since she delivered the face-to-face Dietitian consultations. She phoned the women within a day of their baseline measures to inform them of their group assignment.

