### Sample size

The sample size calculation was based on the main outcome measure of body weight. Observational studies of women in this age group in the Australian population have demonstrated a mean (SD) weight gain of 1.04 (4.7) kg over a two-year period [22]. Given both intervention groups were comprised of equal numbers of healthy weight and overweight women and presuming the overweight women would meet the intervention goal of losing 5 kg^a^ in the first 12 months and the healthy weight women would show zero weight change, the net weight change should be a 2.5 kg weight loss in the MI group by the end of phase 1. Based on the Australian data of net weight gain in the general population of mid-age women managing their weight by self-directed means [21], we would expect a mean (SD) net weight gain of 0.5 (4.7) kg per year in our SDI (control) group. This would give an expected difference between the two groups of 3.0 kg after 12 months (end phase 1) and 3.5 kg after 24 months (end phase 2). Assuming equal sample sizes, to detect a difference in weight between groups of 3.5 kg with 80% power and a significance level of 0.05, a sample size of 22 women was required for each group. Allowing for an attrition rate of 20% by the end of 24 months, a total sample size of 55 women is required.

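### BMI category stratifies the randomisation but is not a term in the primary weight ANCOVA; adding it is a free, modest gain in precision

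*Protocol article*

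**What the plan says.** **Randomisation.** The abstract describes participants as "stratified according to Body Mass Index (BMI) category". Under Randomization, blinding and quality assurance, "The sequence was divided into two separate lists", one per BMI category, in blocks of six, and the researcher "allocated the participant to the next vacant number sequence on either the healthy weight list or the overweight list as appropriate".

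**Goals.** Under Goals of the intervention, healthy-weight women are to hold their weight within 1 kg and overweight women are to lose up to 7%. This applies in both arms.

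**Primary analysis.** Under Data analysis, ANCOVA examines "whether the intervention groups differed significantly in weight at each of 12 and 24 months after adjusting for baseline weight". Baseline weight is the only covariate named. The same paragraph ends: "Results will be stratified for baseline BMI category".

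**Planning assumptions.** Under Sample size, the MI effect is built "presuming the overweight women would meet the intervention goal of losing 5 kg" while "the healthy weight women would show zero weight change", so that "the net weight change should be a 2.5 kg weight loss in the MI group by the end of phase 1". The self-directed (SDI) arm is given a single mean gain of 0.5 kg per year with SD 4.7 kg, not split by category.

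**The concern.** A factor used to restrict the randomisation, and expected to predict the outcome, belongs in the primary model. If it is left out, the balance that stratification creates is not credited in the standard error, which comes out somewhat too large. Here the factor also decides which weight goal a woman receives, with a sharp switch at BMI 25.

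Baseline weight is only a partial stand-in. It mixes in height, it is continuous where the goal is a step, and as a main effect it cannot represent a treatment effect that differs by category. The plan's own figures imply such a difference. At 24 months, taking SDI as +1 kg in both categories and the MI loss as maintained, the effect is 1 kg in healthy-weight women (0 versus +1) and 6 kg in overweight women (−5 versus +1), averaging 3.5 kg.

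At stake are some power in a small trial and a clear basis for any statement about how the effect differs between categories.

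**Working it through.** **Inputs.** From the article: difference 3.5 kg, SD 4.7 kg, 22 per group, alpha 0.05, category gap 5 kg in the MI arm. Assumed: 4.7 kg is the SD within category; the categories are equal in size; mean baseline weight differs between categories by D = 10 to 13 kg; within-category SD of baseline weight is s = 4 to 8 kg. The article gives only the overweight mean, 73 kg.

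**The plan's own figure.** n per group = 2 × [4.7 × (z_alpha + z_power) / 3.5]². This gives 22.3 for a one-sided 0.05 test and 28.3 for a two-sided one. The stated 22 therefore fits only a one-sided, unadjusted comparison, which is a separate matter. 44 / 0.80 = 55 reproduces. The two-sided level is used below.

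**Variance due to category.** Let M be the main-effect part and I the group-by-category part.

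- Scenario A, gap of 5 kg in MI and none in SDI (the plan's assumption): the average gap is 2.5 kg, so M = 1.25² = 1.56. The total averaged over arms is 2.5² / 2 = 3.125, so I = 1.56.
- Scenario B, gap of 5 kg in both arms: M = 2.5² = 6.25 and I = 0.

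**What baseline weight absorbs.** The share of M explained by baseline weight is ρ² = (D/2)² / [(D/2)² + s²]. With D = 13 and s = 4 this is 42.25 / 58.25 = 0.73. With D = 10 and s = 8 it is 25 / 89 = 0.28.

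**Residual variance.** Weight only: 22.09 + I + M(1 − ρ²). Adding category: 22.09 + I. Adding the interaction: 22.09.

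**Power** = Φ[3.5 / (SD × √(2/22)) − 1.96].

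| Model | A: SD (kg) | A: power | B: SD (kg) | B: power |
|---|---|---|---|---|
| Baseline weight only | 4.91 to 4.98 | 64 to 66% | 4.88 to 5.16 | 61 to 66% |
| + category | 4.86 | 67% | 4.70 | 69% |
| + category and interaction | 4.70 | 69% | 4.70 | 69% |

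This large-sample formula does not charge for lost degrees of freedom. In scenario A it gives gains of about 1 to 2 points for category and 4 to 5 with the interaction. In scenario B the gain is about 3 to 8 points.

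**Simulation of the ANCOVA, 22 per arm.**

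- Scenario A: 62.5% with weight only, 62.7% with category, 65.5% with the interaction. With height assumed at 1.64 m (SD 0.06 m): 64.7%, 65.5% and 68.4%. The mean standard error falls from 1.48 to 1.42 kg.
- Scenario B (D = 13, s = 6): 62.3% with weight only and 67.1% with category. Type I error is 4.2% without the stratum and 4.9% with it.
- Gap of 2.5 kg in MI only: 66.4%, 66.0% and 66.7%, which is no real gain.
- No gap: 67.9% falls to 67.4%. A loss of up to about 1 point is a fair allowance.

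**Split-sample tests, if they were used to compare categories.** Assume 11 per arm per category, SD 4.7 kg, an unadjusted two-sided t-test and a true effect of 3.5 kg in both categories. Each test has 38% power, so the chance that exactly one is significant is 2 × 0.38 × 0.62 = 47%.

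**The case against.** The strongest reply is that the omission costs almost nothing. In the plan's own scenario the category main effect adds under 1 point in simulation, and most of the gain comes from the interaction. That gain needs the full 5 kg gap, which rests on overweight MI women meeting their goal. At half the gap it vanishes. The test without the stratum is valid and, if anything, slightly conservative. All of this stands.

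Three stronger readings are tempting, and the article does not support them.

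- A reader might infer that a 5 kg category difference is left in the error term. The 5 kg and 0 kg figures are used for the MI arm only, which makes the average gap 2.5 kg, and baseline weight already takes up between about a quarter and three quarters of the main effect.
- A reader might compare an SD of 5.02 kg (the root of 22.09 + 3.125) with 4.7 kg and say that 12% of the variance is category structure. That describes a model with no covariate, which is not the planned one.
- A reader might infer that p-values for weight will be compared across subsets. The article does not say so. Its wording about determining whether results differ by category belongs to visceral adipose tissue, and the testing of stratified results may be set out in a fuller plan.

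What the reply does not remove is that the primary model is stated with its covariate and the stratum is not in it. The sentence on stratified results does not say otherwise.

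**Conclusion.** The point holds as a free improvement. The randomisation is stratified by BMI category and the goals depend on it, but the overall weight comparison at 12 and 24 months is not adjusted for it. The consequence is a modest loss of precision and a slightly conservative test. It is neither bias nor an inflated type I error.

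In simulation under the plan's assumptions, adjusting gains under 1 power point with a main effect and about 3 with the interaction. If the gap holds in both arms, which is plausible because SDI women receive the same category-specific goals, the gain is about 3 to 8 points. If there is no gap, up to about 1 point is lost. These sizes rest on 22 per arm, 3.5 kg, a two-sided 0.05 level, 4.7 kg as the within-category SD, and assumed heights and healthy-weight baseline values. They were worked at the 24-month difference; the planned 12-month difference is smaller, 3.0 kg.

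**What to change.** Add BMI category to the ANCOVA of weight at 12 and 24 months, alongside group and baseline weight, and take the primary group effect from that model. Include the group-by-category term, and report the category-specific effects and the interaction with 95% confidence intervals from the same model instead of from separate split-sample tests.

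State in advance how the overall effect is averaged over categories. Equal weights would match the half-and-half mix in the sample size calculation; the observed proportions are also defensible. Reword the sentence on stratified results to say what it adds to the overall comparison.

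The cost is two model terms, two degrees of freedom and no new data, since BMI category is recorded for every woman at allocation.
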